**SECTION 1: ADMINISTRATIVE INFORMATION****1. Title and trial registration****1.a Title**

Title: Statistical analysis plan for Co-venture Trial: A Cluster Randomized Trial Investigating the Effects of Selective Intervention on Adolescent Cognitive Development and Addiction

Sub-Title: Statistical analysis plan for Co-venture Trial

**1.b Trial registration**

Trial registration number: NCT01655615

**2. Statistical Analysis Plan version**

Version 1.1    Date: April 15, 2021

**3. Protocol version**

This document has been written based on information contained in study protocol Version 2.0 October 31th, 2016 (Version 1.0 August 2, 2012)

**4. Description of this document**

This document describes statistical analysis plan (SAP) for Co-Venture trial. The SAP was developed according to guidelines found in ICH E9. This SAP contains more technical and detailed elaboration of principal features of the analysis describes in the protocol, and includes procedures for executing the statistical analysis of the primary and main secondary variables. Exploratory analyses not identified in the SAP will be clearly identified in the reporting as well as any deviation in the analyses from this original SAP.

The SAP should be executed once the trial database lock (DBL) has been achieved. Analyses will not be blind for the randomization group. All the analyses will strictly follow the Statistical Analysis Plan (SAP) described in this document. Analyses will be done under the responsibility of the trial statistician at the Data Coordinating Center (Applied Clinical Research Unit (ACRU), Hôpital Sainte-Justine, Montreal). The study Principal Investigator

 International Conference on Harmonisation of Technical Requirements for Registration of Pharmaceuticals for Human Use. ICH Harmonised Tripartite Guideline: Statistical Principles for Clinical Trials E9. London, England: European Medicines Agency; 1998.

and the Steering Committee will be kept blind to the randomization group until final disclosure of the study results.

#### 4. Statistical Analysis Plan revisions

| Protocol version | Updated SAP version | Section number | Description of and reason for change | Date changed |
|------------------|---------------------|----------------|--------------------------------------|--------------|
| 2.0              | 1.1                 |                |                                      |              |
|                  |                     |                |                                      |              |

**SECTION 2: INTRODUCTION****6. Background**

Adolescent substance use is associated with a myriad of immediate and long-term negative consequences. Onset of alcohol use at or before 14 years of age predicts an increased risk of developing alcohol and drug use disorders and other mental health problems, poor academic performance, high school and college drop-out, risky sexual behaviors and injuries. Hazardous drinking patterns such as binge drinking are on the rise among youth worldwide. Statistics in the Canadian province of Quebec are striking and suggest that Quebec youth may initiate drinking earlier and show an accelerated growth in substance use relative to other North American youth. By grade 8, 44.4% of Quebec students have consumed alcohol, compared to the Canadian national average of less than 20% and 29.3% in the USA. By the end of high school, 76.5% of Quebec students report binge drinking and about 10% screen positive for a substance use disorder.

Adolescent brains may be particularly susceptible to damage from alcohol use due to the significant neuro-maturation occurring throughout this period. This has been shown to be true in rodent models, where alcohol-neurodegeneration is more severe in adolescent than adult brains. Enhanced susceptibility to alcohol-induced neurodegeneration has also been observed in human adolescents.

Alcoholism in adulthood has been associated with cognitive impairments across multiple domains. Moderate deficits have also been reported in adolescents with less chronic alcohol use disorders, including impairments in verbal and non-verbal memory, attention, executive functions, and visuospatial performance. In addition, cognitive deficits have been observed in the non-problematic, social drinking population, with the suggestion that there is a continuum of deficits related to quantity of alcohol consumption. Because the majority of neuropsychological studies with adolescents are cross-sectional, it has been difficult to conclude whether the cognitive abnormalities described are causal or consequential to alcohol misuse. There is a large literature indicating that two major risk factors for adolescent-onset alcohol misuse, namely family history of alcoholism and adolescent onset psychopathology, are associated with brain abnormalities that are also seen in youth with other risk factors for substance use (e.g., externalising personality or psychopathology). There are significant discrepancies across studies examining the prospective associations between cognitive functioning and substance use suggesting that the association between these variables merits further investigation.

Current theories of adolescent brain development propose that a delay in the development of cognitive functioning (sometimes referred to by some as a ‘maturational gap’), as opposed to stable cognitive deficits, may account for the increased risk taking and attentional difficulties seen in adolescence, as well as individual differences between youth. Despite the existence of several longitudinal studies on this topic (e.g., IMAGEN; ), causality remains difficult to establish because lower (or delayed growth in) cognitive functioning might predict early onset substance use, but exposure to substances might further exacerbate cognitive development, particularly in the most vulnerable youth. It is thus important to assess substance use and cognitive functioning at multiple time points in a longitudinal design to examine the developmental sequence and interactions between the uptake and growth in alcohol consumption and cognitive development. In addition, cognitive functioning should be assessed prior to alcohol use onset.

## **7. Study Objectives**

As a primary outcome, this longitudinal cluster-randomized controlled trial will examine the impact of Preventure on reducing addiction risk in adolescents over a 5-year period.

The primary research hypothesis is that fewer high-risk youth will meet criteria for a substance use disorder 4 years post-intervention than high-risk youth in intervention relative to control schools.

The secondary intermediate objectives are to determine whether the short-term impact of the intervention on delaying substance use onset at one year post-intervention, and intervention effects will improve cognitive outcome, as measured by neuropsychological tasks.

Secondary outcomes will examine the intervention effects on mental health outcomes 4 years post-intervention, as measured by self-report mental health screening measures.

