### *1.5 How will the results of this trial be used?*

The results of this trial will be used to clarify the causal pathway between early onset substance use and cognitive development during adolescence, and whether delaying substance use onset can result in improvements in cognitive function and future reduction in risk for addiction. The experimental design of this trial will allow us to examine the course of cognitive development in high risk youth who are assisted in delaying their onset of alcohol use, providing for the first time, an opportunity to tease apart the causes of early onset substance use from the consequences of adolescent substance use from a cognitive-developmental perspective. This study will also allow us to examine how these possible cognitive consequences are implicated in future risk for addiction [82, 83], mental health problems [4, 5], poor academic performance [1, 8], and school drop-out [9, 10]. Findings will dramatically impact on public policy relating to youth substance use and the need for further attention toward prevention services in Canada. Cognitive outcomes relate directly to school-related measures, thus may increase interest in and likelihood of implementation of substance use prevention programmes in schools. Results may also increase interest within the school system, by parents and youth, should it be shown that cognitive function could be improved by targeting substance use risk.

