greater reward bias on the PALP relative to non-bingers with effect sizes (d) for mean differences ranging from .23-.25,  $p=0.05$  [106]. Larger differences are expected as the sample ages and substance use becomes more frequent. A conservative power analysis was conducted to be sure that we could detect effects on cognitive functioning at earlier ages. A sample size of 15 clusters per group with 50 HR adolescents per cluster achieves at least 90% power to detect a difference of at least 3.0 between the group means when the standard deviation is 15.0 (an effect size of 0.20) and the intra-cluster correlation is 0.40 using a false positive error rate of 2.5%.

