Primary outcomes are on the intent to treat sample of youth who meet high risk (HR) personality criteria. To account for within cluster (school) variance, intervention effects will be examined using hierarchical generalized linear modelling (HGLM; using the program HLM 6) [111, 112] using a Bernoulli distribution for the binary primary outcome. Secondary outcome variables will be centred at the 12-month post-test to allow for comparisons between groups (intervention vs. control) after the intervention, and growth terms will be used to detect prevention effects on growth of onset of target behaviour over four years. For the three drinking outcomes, unconditional models from previous trials revealed that more than 10% of systematic variance existed at the between-school level (25-27%), therefore, HLM with robust standard errors will be used to assess intervention effects on the 12-month intercept and growth in drinking from 12-48 months [111]. When significant effects are revealed on growth, STATA (StataCorp, College Station, TX) will then be used to conduct logistic regression analyses testing intervention effects on onset of use at specific time points while controlling for cluster, using tests based on the Huber-White sandwich estimate of variance [110]. The illicit drug use outcome, problem drinking outcomes and cognitive outcomes are not expected to have high inter-class correlations [29]; HGLM will be used to conservatively assess these outcomes, nevertheless. We will also report cluster-level analyses in which individual-level variability is removed and analyses are conducted at the school-level, comparing mean outcomes for intervention (n=15) and control schools (N=15) using one-way repeated measures design with time as repeated measures and intervention as a fixed independent variable following recommendations by [113]. Path analyses will investigate mediational role of substance use and cognitive outcomes risk for addiction.

*2.17 What is the proposed frequency of analyses?*

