## 10. Sample size calculation for the primary outcome

Sample size calculations are conducted according to the sample needed for the primary long-term analyses, namely the onset of substance use disorders 4-years post-intervention in the sub-group of students identified at high-risk in grade 7. As the school (cluster) is the unit of randomisation, the sample size determination accounts for the clustering of students within schools. According to data from a local epidemiologic study and a previous personality-targeted intervention trial, the expected proportion of students with a substance use disorder in grade 11 in the control group is 10%. The minimum detectable reduction is set to 50% (i.e., 10% substance use disorders in grade 11 in the control group versus 5% in the intervention group). Assuming that this proportion per school is approximately normally distributed (i.e., 95% of the schools would fall within two standard deviations of the mean, 10%, 7 %), we obtain a between-cluster coefficient of variation,  $k$ , of 0.35. In addition, we expect 50 students per school (40-45% of the full sample) to be identified as high-risk (average cluster size of 50), following previous personality-targeted intervention studies. With these assumptions (using formula 7.7,), the number of schools (clusters) per arm needed to detect a 50% reduction in the proportion of drinkers (i.e., from 10% to 5%) with 80% power and a false positive error rate of 2.5% is 15, giving a total of 30 schools or approximately 1500 high-risk students. We plan to recruit two additional schools ( $30 + 2 = 32$  schools total) to account for potential attrition at the school-level.

For the secondary outcomes (other measures of substance use, mental health and cognition), we will use the observed effect sizes from the IMAGEN study on 2000 14 year-old European participants who completed neuropsychological assessments. Binge drinkers showed reduced IQ and a greater reward bias on the Passive Avoidance Learning Paradigm^45 relative to non-bingers where observed effect sizes ( $d$ ) for these mean differences ranged

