from 0.23-0.25. Larger mean differences are expected in our study since our follow-up is longer. We also expect more cognitive development to take place in intervention participants as we expect reductions in substance use following the intervention to promote their cognitive development. Thus, we expect differences in cognitive development to increase over time between intervention and control groups. A sample size of 15 clusters per group with an average of 50 high-risk adolescents per cluster will achieve at least 90% power to detect a difference of at least 3.0 between the group means of cognitive functioning with a standard deviation of 15.0 (an effect size of 0.20)  and an intra-cluster correlation of 0.40 using a false positive error rate of 2.5%.

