**26.c Analysis methods used for the secondary outcomes**

Using a similar method, secondary analyses will examine the 12-month intercept and the linear slopes (i.e. growth) from 12 - 48 months post-intervention between intervention and control conditions in alcohol and drug use behaviours. Growth terms will be used to detect prevention effects on growth in substance use behaviours over 4 years.

Similar analyses will be carried out for secondary and exploratory outcomes presented in Appendix 3.

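### The SAP tests cognition only by comparing arms, which cannot show that delaying substance use is what protects it, and the planned 0.20 SD arm difference is a drinker-versus-non-drinker figure

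*Combined protocol and SAP*

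**What the plan says.** The documents ask two questions about cognition.

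- **Does the intervention improve it?** Both hypotheses in protocol 1.2 are worded as effects of the intervention, and SAP 8 and 11 (efficacy and superiority, including secondary outcomes) agree.
- **Is delayed or reduced substance use the reason?** SAP 7 asks "whether the short-term impact of the intervention on delaying substance use onset at one year post-intervention, and intervention effects will improve cognitive outcome". Protocol 1.5 says the results will "clarify the causal pathway between early onset substance use and cognitive development during adolescence". SAP 10 builds on the same mechanism: "we expect reductions in substance use following the intervention to promote their cognitive development".

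For analysis, SAP 26.c (secondary outcomes) compares arms on the 12-month intercept and the 12-48 month slope of alcohol and drug use, then adds: "Similar analyses will be carried out for secondary and exploratory outcomes presented in Appendix 3". Cognition enters by that sentence. SAP 26.c (sensitivity analyses) announces an examination of mechanisms but lists imputation, a per-protocol analysis and an interaction with high-risk status. Protocol 2.16 does plan mediation, in one sentence: "Path analyses will investigate mediational role of substance use and cognitive outcomes risk for addiction". The SAP has no counterpart.

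For planning, SAP 10 starts from an observational contrast: "Binge drinkers showed reduced IQ and a greater reward bias on the Passive Avoidance Learning Paradigm". Protocol 2.11 words the size as "relative to non-bingers with effect sizes (d) for mean differences ranging from .23-.25". Both documents then plan for 0.20 SD between arms (3.0 points, SD 15), with at least 90% power at ICC 0.40. The SAP adds: "Larger mean differences are expected in our study since our follow-up is longer".

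**The concern.** The arm contrast has one null hypothesis: the intervention changes cognition by no route. The intervention combines psycho-education, motivational enhancement and CBT, and one of its target traits is impulsivity (protocol 2.2). Response inhibition is a cognitive outcome. A direct route from training to test score is therefore possible, and a difference between arms would not say which route produced it.

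The planning figure has a related problem. A difference between drinkers and non-drinkers becomes a difference between arms only in proportion to how far the intervention changes the share who drink.

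At stake is the interpretation of the secondary aim. A positive result could be credited to delayed substance use without evidence for that step. A null could be taken as evidence against the mechanism when, under most of the assumptions below, the contrast had little chance of showing it.

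**Working it through.** **Step 1. The plan's own power figure.** Inputs from SAP 10: 15 schools per arm, 50 students per school, difference 0.20 SD, ICC 0.40, error rate 2.5% (sidedness not stated).

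- Design effect = 1 + 49 × 0.40 = 20.6. Effective n per arm = 750 / 20.6 = 36.4.
- SE = √(2 × 20.6 / 750) = 0.234 SD. Ratio = 0.20 / 0.234 = 0.853.
- Power, 2.5% two-sided: Φ(0.853 − 2.241) = 8.3%. Power, 2.5% one-sided or 5% two-sided: Φ(0.853 − 1.960) = 13.4%. A noncentral t on 28 df gives 7.8% and 12.8-13.1%.

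The stated 90% is not reproduced. Treating four visits as 200 independent observations per school still gives only 8-14%, because the between-school term dominates. About 90% needs an ICC near 0.004 (two-sided) to 0.01 (one-sided).

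**Step 2. The arm effect implied by the mechanism.** Implied arm effect = d (binge v non-binge) × control binge prevalence × relative reduction.

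- d = 0.23-0.25 (protocol 2.11, SAP 10).
- End-of-school binge prevalence: 0.856 × 0.798 = 68.3% (protocol 1.1), or 76.5% (SAP 6).
- Relative reduction in use: 30-80% (protocol 1.2).
- Lowest: 0.23 × 0.683 × 0.30 = 0.047 SD. Highest: 0.25 × 0.765 × 0.80 = 0.153 SD. On the SD-15 scale that is 0.7 to 2.3 points, against the planned 3.0.
- Abolishing binge drinking, at d = 0.25: 0.25 × 0.683 = 0.17 SD, or 0.25 × 0.765 = 0.19 SD. Both are below 0.20.
- d needed for 0.20 between arms at 68.3% prevalence: 0.20 / (0.683 × 0.80) = 0.37, up to 0.20 / (0.683 × 0.30) = 0.98.

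**Step 3. Power for that effect.** 15 v 15 schools of 50, SE = √(2 × (ICC + (1 − ICC)/50) / 15), noncentral t on 28 df, two-sided 5% (SAP 15). ICC 0.40 is the SAP's value. ICC 0.09 is the documents' value for problem drinking. ICC 0.05 and 0 are assumptions.

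| ICC | SE | 0.047 SD | 0.137 SD | 0.153 SD |
|---|---|---|---|---|
| 0.40 | 0.234 | 5% | 9% | 10% |
| 0.09 | 0.120 | 7% | 20% | 23% |
| 0.05 | 0.096 | 8% | 28% | 34% |
| 0 | 0.052 | 14% | 73% | 82% |

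The middle column is 0.25 × 0.683 × 0.80.

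**The case against.** The strongest reply is that the arm contrast tests the hypotheses as written. Protocol 1.2 compares participants by randomised condition, SAP 8 and 11 do likewise, and SAP 7 itself mentions intervention effects. This stands. A reader might infer that the contrast is invalid or has an inflated false-positive rate. It does not: if training acts directly on cognition, the null is false, and rejecting it is a correct finding about the total effect. The limit lies in attribution.

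A reader might also infer that mediation was never planned. Protocol 2.16 does plan it, and SAP 28 allows labelled exploratory work. But that sentence names addiction risk as its endpoint and gives no model, time order or confounders. A path model for cognition would have to be written, not merely restored.

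Third, it is tempting to say the trial could not detect the mechanism at all. The documents do not support that. With an 80% reduction and ICC 0, power is 73-82% at d = 0.25, and protocol 2.16 does not expect high school-level correlation for cognition. Both documents expect a larger d with longer follow-up, though without a figure. High-risk students may binge more than Quebec students generally, other drugs may contribute, and baseline adjustment could add precision.

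Finally, mediation gives up the protection of randomisation. SAP 6 notes that lower cognitive functioning may itself predict early use. This stands and must be stated with any path estimate. SAP 16 also limits secondary endpoints to supportive, exploratory use.

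**Conclusion.** The point holds as a gap in what the secondary aim can conclude. The SAP's only specified test of cognition estimates the total effect of the intervention. It cannot show that delaying substance use is what protects cognition, and no SAP analysis does.

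The 0.20 SD planning figure carries a drinker-versus-non-drinker difference over to the arms undiluted. The implied effect is about 0.05-0.15 SD, assuming binge drinking is the sole mediator, d stays at 0.23-0.25, the observational difference is wholly causal, and the two-year reduction persists to the end of school. Low power for that effect is secure at the SAP's ICC of 0.40 (about 5-10%). It is 8-34% at ICC 0.05, and ranges from 14% to 82% at ICC 0.

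The failure of the 90% claim is a separate matter and needs none of the mechanism assumptions: SAP 10's own inputs give about 8-13%.

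**What to change.** 1. **SAP 26.c (secondary outcomes).** Label the cognitive arm contrast as the total effect of the intervention on cognition, and state that it will not be interpreted as a test of whether delaying substance use protects cognition.
2. **Same section.** Add one pre-specified secondary path model: arm → substance use at 12 and 24 months → cognition at 36 and 48 months, adjusted for baseline cognition and baseline use, with school clustering. Report direct and indirect effects with intervals, and state that they rest on no unmeasured mediator-outcome confounding. If cognition has already been examined by arm when this is written, say so and label the model exploratory under SAP 28.
3. **SAP 10.** Keep 0.20 SD as the historical design basis, but state that it derives from a user-versus-non-user comparison. Give the implied arm effect of about 0.05-0.15 SD with its assumptions, and correct the 90% power claim for the stated ICC.

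The cost is wording plus one model on data the visit schedule already collects at every wave. Sample size and the primary analysis do not change. There are two real drawbacks: the path estimate carries an untestable assumption that the SAP's own background makes doubtful, and the stated sensitivity of the trial for cognition becomes less favourable.
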